# Clinical and cost-effectiveness of guided internet-based interventions in the indicated prevention of depression in green professions (PROD-A): study protocol of a 36-month follow-up pragmatic randomized controlled trial

**DOI:** 10.1186/s12888-019-2244-y

**Published:** 2019-09-09

**Keywords:** Prevention, Depression, Internet- and mobile-based interventions, Green professions, RCT

## Abstract

**Background:**

People in green professions are exposed to a variety of risk factors, which could possibly enhance the development of depression. Amongst possible prevention approaches, internet- and mobile-based interventions (IMIs) have been shown to be effective and scalable. However, little is known about the effectiveness in green professions. The aim of the present study is to examine the (cost-)effectiveness of a tailored IMI program for reducing depressive symptoms and preventing the onset of clinical depression compared to enhanced treatment as usual (TAU+).

**Methods:**

A pragmatic randomized controlled trial (RCT) will be conducted to evaluate a tailored and therapeutically guided preventive IMI program in comparison to TAU+ with follow-ups at post-treatment (9 weeks), 6-, 12-, 24-, and 36-months. Entrepreneurs in green professions, collaborating spouses, family members and pensioners (*N* = 360) with sufficient insurance status and at least subthreshold depression (PHQ-9 ≥ 5) are eligible for inclusion. Primary outcome is depressive symptom severity (QIDS-SR16). Secondary outcomes include incidence of depression (QIDS-SR16), quality of life (AQoL-8D) and negative treatment effects (INEP). A health-economic evaluation will be conducted from a societal perspective. The IMI program is provided by psychologists of an external service company and consists of six guided IMIs (6–8 modules, duration: 6–8 weeks) targeting different symptoms (depressive mood, depressive mood with comorbid diabetes, perceived stress, insomnia, panic and agoraphobic symptoms or harmful alcohol use). Intervention choice depends on a screening of participants’ symptoms and individual preferences. The intervention phase is followed by a 12-months consolidating phase with monthly contact to the e-coach.

**Discussion:**

This is the first pragmatic RCT investigating long-term effectiveness of a tailored guided IMI program for depression prevention in green professions. The present trial builds on a large-scale strategy for depression prevention in green professions. The intended implementation of the IMI program with a nationwide rollout has the potential to reduce overall depression burden and associated health care costs in case of given effectiveness.

**Trial registration:**

German Clinical Trial Registration: DRKS00014000. Registered on 09 April 2018.

## Background

Major depressive disorder (MDD) is a highly prevalent disorder in the general population: a 12-month prevalence of MDD amounts to 6.7% [1], while lifetime prevalence is estimated at 10.6 to 19.8% [2]. MDD is associated with substantial functional impairment [3, 4] and has been identified as a leading cause of global disease burden [5]. In addition to the high individual burden, the socioeconomic costs associated with MDD and its comorbid physical and psychiatric disorders due to medical use, absenteeism, loss of productivity at work and suicide, are enormous [6].

An estimation of prevalence rates in the specific target group of green professions in Germany has yet to be conducted. However, people in green professions are exposed to a variety of risk factors, which might increase vulnerability for developing MDD. Risk factors include financial pressure, high administrative workload, long working hours, high stress levels, part-time jobs off the farm, health problems and preceding work accidents [7, 8], as well as continuous exposure to pesticides [8–10]. In addition, an increased risk of suicide in the agricultural sector was reported across different countries e.g. in England and Wales [11, 12], the USA [13–15], Australia [16, 17], and Brazil [9]. Based on given risk factors and risk of suicide, preventive measures are highly indicated.

Psychological interventions for subthreshold depression as indicated prevention have been shown to significantly reduce depressive symptom severity [18]. Additionally, such interventions might even prevent the onset of major depression [18, 19]. Thus, preventive interventions can have a substantial role in reducing overall depression burden in green professions.

Although face-to-face psychotherapy represents an effective treatment option, impact of such on-site offers is restricted. MDD is still an underdiagnosed and undertreated condition with only approximately 50% of persons with 12-month MDD receiving some kind of treatment, and only approximately 20% of affected persons receiving an appropriate treatment concordant with treatment guidelines [4]. In Germany, availability of on-site psychotherapy is restricted by long waiting times and is furthermore lower in rural areas than in urban areas [20].

Internet- and mobile-based interventions (IMIs) have already shown to be effective in reducing subthreshold depression [21–25] and thus, pose a suitable alternative treatment option to on-site psychotherapy. While short-term effectiveness of IMIs regarding depression severity at post-treatment is well established, studies on long-term effectiveness are scarce and yield inconsistent evidence [26].

IMIs constitute a promising approach for providing an effective and easily accessible prevention offer in routine health care [27, 28]. As IMIs can be used independently of time and place, they are easily accessible even in rural areas and have the potential to increase acceptance and utilization of psychological interventions [29]. Currently, little is known about acceptance, effectiveness or utilization of IMIs in the specific target group of green professions.

To improve the delivery situation in rural areas, and specifically for the target group of green professions, this study will be conducted in the framework of a national depression prevention program for people in green professions, implemented by the Social Insurance for Agriculture, Forestry and Horticulture (SVLFG, http://www.svlfg.de/). The SVLFG currently establishes a comprehensive prevention model project (“With us in balance”) for their insurees with the offered services of guided IMIs, personalized tele-based coaching as well as on-site prevention group workshops, provided by different service providers in the health care sector. Parallel to a nationwide rollout, the single internet- or telephone-based prevention offers will be evaluated in randomized controlled clinical trials (RCTs) in order to establish evidence on the clinical and cost-effectiveness. Eligible for this trial are policyholders of the SVLFG who are entrepreneurs, family members, spouses or have retired in one of the three sectors of agriculture, forestry or horticulture (referred to as “green professions”).

In the present study, IMIs for the prevention of depression provided by the health care company GET.ON will be evaluated regarding effectiveness and cost-effectiveness. GET.ON institute offers scientifically evaluated IMIs for different mental health problems (depressed mood in general or in the context of diabetes mellitus, insomnia, stress, panic and agoraphobic symptoms and harmful alcohol use). Even though these IMIs differ regarding their focus on mental health problems, they will be evaluated as part of a depression prevention program. The underlying idea follows the rational of a transdiagnostic approach: Transdiagnostic research has already yielded promising evidence that treatment protocols based on transdiagnostic maintaining factors and treatment concepts can lead to symptom reduction comparable to disorder-specific treatments [30, 31]. This already indicates that psychological interventions do not necessarily need to be disorder-specific and labeled accordingly to achieve symptom alleviation.

Especially in prevention context, it is desirable to reach and provide preventive interventions for a large population sample. Low adherence and high dropout rates [32, 33] restrict impact of IMIs. Treatment credibility and treatment motivation have been shown to predict treatment adherence [34, 35]. Thus, measures to increase motivation or treatment credibility are highly desirable, as they improve participation in preventive interventions and reduce dropout rates of participants [36–39]. The (cost)effectiveness of this tailored and guided prevention approach is especially interesting, as it leaves room for greater emphasis on personal interest and treatment motivation in the selection procedure of an appropriate intervention. Further, stigma against depression can still be a common issue in rural areas [40, 41]. This patient-centered and complaint-based approach also has the potential to improve the uptake of IMIs especially for depression prevention, by avoiding the exclusive label of “depression” and potentially associated stigma.

### Objective and research question

The aim of the present study is to investigate whether a tailored IMI program targeting a variety of specific complaints associated with clinical depression is useful in reducing depressive symptoms and preventing onset of clinical depression as compared to enhanced treatment as usual (TAU+) within a 36-month follow-up period. We propose, that depressive symptomology will be reduced to a greater extent in the intervention group (e.g. IMI program) than in the control condition (e.g. TAU+) post-treatment (T1). The following research questions will be investigated in this pragmatic randomized controlled trial over a follow-up period of 36-months:
Is the IMI program effective in reducing depressive symptom severity compared to TAU+?Is the IMI program effective in preventing the onset of clinical depression as compared to TAU+?Is the IMI program effective in reducing various mental health outcomes (e.g. stress, anxiety, insomnia) compared to TAU+?Is there a differential or rather an undifferentiated, general effect of specific IMIs on different mental health outcomes?Is the IMI program superior in terms of cost-effectiveness and QALY health gains compared to TAU+?Which variables moderate and mediate the effects of the IMI program?What is the level of intervention satisfaction, adherence and acceptance to the IMI program?Are there negative effects of the IMI program?

## Methods

### Study design

A two-armed pragmatic randomized controlled trial (RCT) will be conducted comparing the clinical and cost-effectiveness of a tailored, guided IMI program to a control group (CG) receiving enhanced treatment-as-usual (TAU+). Primary and secondary outcomes will be assessed over a period of 36 months. Assessments will take place at baseline (T0), post-treatment (nine weeks, T1), as well as at 6-month (T2), 12-month (T3), 24-month (T4) and 36-month (T5) follow-up.

This clinical trial has been approved by the ethics committee of University of Ulm (No. 454/17) and will be reported in accordance with the Consolidated Standards of Reporting Trials (CONSORT) Statement 2010 and the extension for reporting pragmatic trials [42–44] as well as the guidelines for executing and reporting internet intervention research [45]. This trial protocol was created according to SPIRIT guidelines [46, 47]. This study is registered in the German clinical trial register under DRKS00014000.

### Participants & procedure

#### Inclusion and exclusion criteria

We will include a) agriculturists, foresters and horticulturists with sufficient insurance status of a social insurance company (SVLFG) in Germany. The study is accessible for entrepreneurs, collaborating spouses and family members as well as pensioners who do no longer contribute to the production process with sufficient insurance status. Participants are required to b) be age 18 or above, c) show an indication for at least subthreshold depression (PHQ-9 ≥ 5), d) have internet access, and e) be willing to give informed consent. Participants will be excluded a) if they are currently receiving psychotherapy (self-report), b) if they are not able to distance themselves from suicidal ideation (not able to sign a non-suicide contract), and c) if they have comorbid chronic pain symptomology (Chronic Pain Grade Questionnaire (CPG) ≥ Grade II + chronic pain longer than six months) and prefer to participate in the parallel clinical trial PACT-A on improving pain related distress in people with chronic pain (Terhorst Y, Braun L, Titzler I, Buntrock C, Freund J, Thielecke J, et al.: Effectiveness and cost-effectiveness of an acceptance and commitment therapy to improve chronic pain-related disability in green professions (PACT-A): study protocol of a 36-month follow up pragmatic randomized controlled trial, in preparation).

#### Recruitment

This clinical trial is embedded in a large-scale mental health initiative of the SVLFG with the aim to improve the prevention of mental health problems in agriculturists, foresters and horticulturists. Participants are recruited via several articles in the members-journal (quarterly circulation 1.3 million), postal mailings as well as information on associated websites. Since interested persons are provided with various ways of contact (via postal return element, fax, e-mail, telephone) and an alternatively direct access to the screening assessment (via QR-Code and URL), a low-threshold access into the study is provided. Recruitment started in January 2018 and was concluded in April 2019 (Fig. 1).

**Fig. 1 Fig1:**
[figure not shown]
Overview of study procedure

#### Assessment of eligibility and randomization

People are screened for eligibility via an online screening questionnaire. Screening includes online questionnaires to assess the presence and the severity of depressive (PHQ-9 ≥ 5) and chronic pain symptomology (CPG ≥ Grade II + chronic pain longer than six months), as well as possible suicidal ideation. Online questionnaires include self-report of age, insurance status, and current psychotherapy. If the eligibility criteria are fulfilled, applicants will receive an online information letter including detailed information about study procedure and informed consent. They will be informed that they can withdraw from the intervention and/or study at any time without any negative consequences. After giving informed consent, participants will enter the study and complete baseline assessment (T0).

Subsequently, participants will be randomly allocated to intervention or control condition and will be informed about group membership via e-mail. Randomization will take place at an individual level. Randomization will be conducted by a person who is blind regarding all processes within the intervention. Whereas blinding of participants is not possible, data collectors are blinded regarding group membership. Group membership is only known by the persons administering allocated treatments to participants. The automated web-based programme sealed envelope (www.sealedenvelope.com) is used to perform permuted block randomization with randomly arranged block sizes (8, 10, 12) and an allocation ratio of 1:1.

Written informed consent for participation in online-assessments will also be obtained from e-coaches. No eligibility criteria are applied by the study team for selection and assignment of e-coaches. E-coaches are employed, assigned, guided and supervised by the GET.ON institute regarding their task of counselling the study participants.

### Intervention

#### Intervention condition

Participants in the intervention group (IG) will be transferred to the service provider GET.ON to get access to a tailored and guided IMI program with the option of conducting one of six available IMIs. The IMI program consists of a 3-step intervention entailing (1) *psycho-diagnostic assessment*, (2) *participatory selection of a suitable (guided) IMI* and (3) *access to IMI*. The IMI program will be carried out by the external service company GET.ON without involvement from the study team. Thus, the GET.ON institute is responsible for providing an adequate care of the participants against the background of the psycho-diagnostic assessment and the information they receive in the course of patient contact. This includes for example the handling of adverse events in the course of e-coaching. The study team evaluates in this setting the standard procedure of the GET.ON institute for the allocation of the different trainings and the treatment of participants in the course of the IMI program.
The *psycho-diagnostic assessment* is based on a selection of self-report questionnaires measured as part of baseline assessment (T0). Relevant baseline assessment values are transmitted electronically to GET.ON for each participant to allow for psycho-diagnostic assessment based on allocation rules applied in supply routine of GET.ON. Each participant is assigned to a personal e-coach after signing in to the intervention platform. E-coaches are trained psychologists, who are in training for a further qualification in psychotherapy and supervised by an experienced psychological therapist.Participants are contacted via telephone or private message function on the intervention platform by their personal e-coach for *participatory selection of a suitable (guided) IMI.*
The IMI program entails six different IMIs with the aim to reduce subthreshold depression by focusing on depressed mood in general (*GET.ON Mood Enhancer*) or in the context of a comorbid diabetes mellitus (*GET.ON Mood Enhancer Diabetes*), by improving sleep quality (*GET.ON Recovery*), or by reducing subjective stress load (*GET.ON Stress*), panic symptoms (*GET.ON Panic*), or harmful alcohol use (*GET.ON Be smart - Drink less*). These interventions have already been shown to effectively reduce depressive symptom severity as primary [23, 25, 48, 49] or secondary outcome [24, 50–55], (Ebenfeld L, Lehr D, Ebert D, Kleine Stegemann S, Funk B, Riper H, et al.: Treating panic on the go: results of a randomized controlled trial evaluating a hybrid online-training for panic and agoraphobia symptoms, in preparation) to prevent the incidence of MDD [24] in other target groups. Moreover, health economic outcome evaluations alongside randomized trials indicate a promising cost benefit [56–59].The type of the IMI is chosen depending on psycho-diagnostic assessment as well as individual participant needs, personal preference and problem areas, which are reported in the course of the conversation.
(3)Directly afterwards *the participants will receive access to the selected IMI*. The IMIs each consist of 6–8 lessons with a duration of 30–60 min. Participants are advised to do one lesson per week. Thus, completion of the intervention is expected to take 6–8 weeks. Depending on the individual pace of the participant, the completion of the intervention can differ. After each lesson, participants get an individualized feedback by their personal e-coach. Guidance is employed to improve adherence of participants and decrease dropout [60]. Depending on the participant’s preference, feedback is given either by telephone or through the internal messaging function of the system in which the online-training is implemented. Afterwards the next lesson is unlocked for the use. In exceptional cases, it is possible to switch the training directly if the assigned tailored intervention is perceived to be unsuitable by the participant.

The IMIs are based on principles of cognitive behavioural therapy (*GET.ON Mood Enhancer*, *GET.ON Mood Enhancer Diabetes, GET.ON Recovery, GET.ON Panic, GET.ON Be smart - drink less)* and on the transactional model of stress and coping [61] (*GET.ON Stress).*
*GET.ON Mood Enhancer* aims to reduce depressed mood by promoting the uptake of positive activities and the learning of problem-solving strategies [62].*GET.ON Mood Enhancer Diabetes* is an adaptation of *GET.ON Mood Enhancer* and aims to reduce depressed mood in the context of diabetes mellitus [63].*GET.ON Recovery* is directed towards persons with clinical insomnia complaints and aims to prevent depression by improving participants’ sleep quality, especially through modifying coping behaviour regarding rumination and worrying. This is achieved by assignments such as keeping a diary about ruminating thoughts [64].*GET.ON Stress* aims to reduce depressive symptomology by addressing chronic stress and reducing stress-related complaints. The training instructs to apply problem- and emotion-oriented stress management strategies based on the distinction between solvable and unsolvable problems [65].*GET.ON Panic* aims to reduce depressive symptoms by addressing panic symptoms and agoraphobia. Participants are instructed to perform in-vitro and in-vivo exposition. Further, the training comprises information and exercises for coping with negative automatic thoughts and for establishing positive thought processes [66]. If this training is assigned, participants are requested by their consecutive e-coach to clarify their physical symptoms with their GP in advance to rule out the presence of physical illnesses (e.g. cardiovascular diseases). The consultation of the GP is the responsibility of the participant and will not be controlled.*GET.ON Be smart - drink less* was developed to prevent depression by reducing harmful alcohol use in participants, who do not yet meet clinical criteria for alcohol dependence. This training aims to identify emotions and situations associated with alcohol consumption by keeping an alcohol-diary. Further, alternative exercises for actions for coping with negative emotions and problems are included [67]. This training will not be assigned to participants with a hazardous drinking level score of > 20 on AUDIT. In case of AUDIT > 20, participants will receive access to a different training of the portfolio which is most fitting to the complaints and be made aware of their hazardous drinking level by their consecutive e-coach. If interested, the e-coach will provide them with a list of addresses, which they can turn to.

The IMIs are accessible on an online-based intervention platform via either computer (e.g. desktop PC, laptop) or mobile device (e.g. tablet, smartphone). The IMIs contain psycho-educative text material, exercises, and testimonials of exemplary personas, who accompany the participants throughout the intervention. Additionally, interactive elements in form of auditory material and videos clips are included. Audio clips for example are used to convey relaxation techniques, while video clips often serve to give a comprehensible overview about theoretical concepts by experts. Since a focal point is the transfer of content and strategies learned into every-day life, many application examples, instructions and exercises, as well as homework assignments for practising between lessons are included. The content of the online-trainings has been specifically adapted to the target population by inclusion of fitting picture and video material, as well as exemplary testimonials and fictional personas living and working in the agricultural setting. These personas describe the struggle with everyday problems and challenges in green professions, e.g. generational conflicts or handing over of the company to the younger generation.

Subsequent to the completion of the IMI, participants are followed up for 12 months by their individual e-coach to consolidate the treatment effect. During this phase, participants are contacted once a month through telephone or the internal messaging system by their personal e-coach to review their current state, report problems, and give account regarding the transfer of strategies learned into the daily routine.

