### Sample size/power calculation

In this trial, the effectiveness of the IMI program in reducing depression severity is compared to TAU+. The estimation of sample size was based on a meta-analysis by Zhou and colleagues (2016) [26], who reported an effect size of *SMD* = 0.46 [95%-CI: 0.22–0.70] for IMIs in the reduction of subclinical depressive symptoms. In this meta-analysis mostly waitlist control groups where included. Since comparison of IG with TAU+ presumably yields a smaller effect size than comparison with waitlist control group [69], we assumed a conservative effect size of *d* = 0.35 for the present trial. An effect size of *g* = 0.35 [95%-CI: 0.23–0.47] was also reported in a meta-analysis as the effect of psychotherapy on reduction of depressive symptom severity in subthreshold depression with more than a half of the included studies applying care as usual in the CG [18]. Based on prior findings [23–25, 48–55], (Ebenfeld L, Lehr D, Ebert D, Kleine Stegemann S, Funk B, Riper H, et al.: Treating panic on the go: results of a randomized controlled trial evaluating a hybrid online-training for panic and agoraphobia symptoms, in preparation) and the above stated hypothesis, a one-sided t-test (α = 0.05; 1-β = 0.90) with a ratio of 1:1 (IG:CG) is used for power calculation. Power calculation was conducted with G*Power (Version 3.1.9.2) and resulted in an overall sample size of 282 participants. According to a meta-analysis approximately 28% percent of dropout occurred across a sample of studies evaluating efficacy and effectiveness of online-based interventions for depression with therapeutic support [69]. To compensate for an expected dropout of 28%, the present study aims at an overall sample size of 360 participants.

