### Intervention-related outcomes

#### Experience of Working and Technological Alliances

The short version of the Working Alliance Inventory (WAI-SR) [109] will be applied to measure the therapeutic alliance between client and e-coach. The 12-item self-report questionnaire covers the three subscales a) agreement on tasks, b) agreement on goals and c) development of an affective bond. For the German Version, internal consistencies between α = .81 and α = .91 were reported for the subscales and internal consistencies between α = .90 and α = .93 for the total score [109, 110]. Participants in IG will complete the WAI-SR at T1 and T3. Additionally, e-coaches will be requested to complete the 10-item therapist version (WAI-SRT, developed by Adam O. Horvath, http://wai.profhorvath.com/) at T1 and T3. This will allow us to compare how the therapeutic relationship is experienced by client and by e-coach, to gain a differentiated and comprehensive picture of the experienced working alliance. The WAI-SR and the WAI-SRT were adapted in wording for the current study investigating therapeutic alliance in guided IMIs. The items were changed to refer to e-coaches instead of therapists and to online-trainings instead of therapy. Additionally, the Technological Alliance Inventory - Online Therapy (TAI-OT) will be administered to assess the technological alliance between client and the online-intervention. The TAI-OT is a new self-report questionnaire developed by Labpsitec (http://www.labpsitec.uji.es/esp/index.php) consisting of 12 items and measures the degree to which the online-program is perceived as helpful in achieving therapeutic goals.

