### Statistical analyses

#### Clinical analyses

All statistical analyses will be performed based on intention-to-treat (ITT) principle. Patterns of missing data will be examined and analyses will be corrected for missing data by applying multivariate imputation according to Van Buuren and Groothuis-Oudshoorn [117]. For those who substantially completed the intervention (at least 80% of the modules) additional per-protocol (PP) analyses will be conducted. Group difference between pre- and post-assessment nine weeks after randomization (T1) in primary outcome will be assessed using generalized linear modelling. Between-group effect size will be reported using standardized mean differences and 95% CIs at all measurement points. Reliable change index (RCI) and number needed to treat (NNT) will be calculated to determine clinical significance. Analysis of long-term effects will be adjusted to the data structure by using e.g. robust estimation of standard errors or mixed effect modelling. Group differences in depression onset will be assessed by calculation of a Poisson regression model. Incidence of clinical depression will be compared in IG and CG by calculation of incidence rate ratio (IRR). Other secondary outcomes like perceived stress, sleep quality, and quality of life will be analysed similarly as primary outcome. Additionally, moderation and mediation analyses will be performed.

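### Neither the T1 model named in the article nor the sample size allows for e-coach clustering in the intervention arm; if the e-coach ICC is above zero, the primary standard error is understated

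*Protocol article*

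**What the plan says.** Randomisation is individual (Assessment of eligibility and randomization). In the intervention arm, "Each participant is assigned to a personal e-coach after signing in to the intervention platform" (Intervention condition). The same section has the coach take part in choosing one of six trainings and give individual feedback after every lesson, so this contact falls largely before T1 at nine weeks. Monthly coach contact follows for 12 months after the training. Controls receive an information letter and links (Control condition), and no coach is described for them.

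For the analysis, the T1 group difference "in primary outcome will be assessed using generalized linear modelling" (Clinical analyses). Dependence is addressed one step later, for another set of comparisons: "Analysis of long-term effects will be adjusted to the data structure by using e.g. robust estimation of standard errors or mixed effect modelling". Coaches are not named in either sentence.

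The Sample size/power calculation section states that "a one-sided t-test (α = 0.05; 1-β = 0.90) with a ratio of 1:1 (IG:CG) is used for power calculation" and "we assumed a conservative effect size of *d* = 0.35 for the present trial", which "resulted in an overall sample size of 282 participants". It adds: "To compensate for an expected dropout of 28%, the present study aims at an overall sample size of 360 participants". It contains no design effect.

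**The concern.** This is a partially nested design. Intervention participants who share a coach share that coach's skill, feedback style and influence on which training is chosen; controls share nothing comparable. Any real difference between coaches adds a variance component to the intervention mean, and recruiting more participants per coach does not average it out. A model that omits this component gives a standard error that is too small, a confidence interval that is too narrow and a p-value that favours the intervention. The power calculation is optimistic for the same reason.

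Coach influence is plausible on the trial's own terms. Coaches are psychologists still in psychotherapy training, the provider assigns them without selection criteria from the study team, guidance is used to support adherence, and the alliance is rated from both sides.

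**Working it through.** **Inputs from the article.** d = 0.35, one-sided α = 0.05, power 0.90, ratio 1:1, 282 analysed, 360 recruited, 28% dropout.

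**Inputs assumed, because the article does not give them.** Number of coaches J = 6, 10 or 20; e-coach ICC ρ = 0 to 0.05; equal caseloads; every evaluable intervention participant has a coach.

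**Step 1: the plan's own figure.** An exact (noncentral t) two-sample calculation with independent observations gives 141 per arm, 282 in total, with power 0.901. The stated figure reproduces with no allowance for clustering.

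**Step 2: evaluable numbers.** 360 × (1 − 0.28) = 259, about 130 per arm. Power at d = 0.35 is then 0.88 with no clustering at all. The fall from 0.90 to 0.88 comes from the dropout allowance (360 is close to 282 × 1.28 = 361, whereas 282/0.72 = 392). It is a separate matter and is not counted here.

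**Step 3: effect of one-arm nesting.**
- Caseload m = 130/J.
- Design effect in the intervention arm DE = 1 + (m − 1)ρ; in the control arm it is 1.
- True SE / naive SE = √((1 + DE)/2).
- Actual one-sided error = 1 − Φ(1.645/ratio).
- Power: noncentral t with the variance multiplied by (1 + DE)/2.

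Example, J = 10 and ρ = 0.02: m = 13; DE = 1 + 12 × 0.02 = 1.24; ratio = √(2.24/2) = 1.058; error = 1 − Φ(1.554) = 0.060; power = 0.84.

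| Coaches | ICC | DE | SE ratio | One-sided error | Power, 259 evaluable |
|---|---|---|---|---|---|
| any | 0 | 1.00 | 1.00 | 5.0% | 0.88 |
| 20 | 0.01 | 1.055 | 1.01 | 5.2% | 0.87 |
| 20 | 0.05 | 1.275 | 1.07 | 6.2% | 0.84 |
| 10 | 0.01 | 1.12 | 1.03 | 5.5% | 0.86 |
| 10 | 0.02 | 1.24 | 1.06 | 6.0% | 0.84 |
| 10 | 0.05 | 1.60 | 1.14 | 7.5% | 0.79 |
| 6 | 0.01 | 1.207 | 1.05 | 5.9% | 0.85 |
| 6 | 0.05 | 2.033 | 1.23 | 9.1% | 0.74 |

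**Step 4: checks.** If all 180 randomised intervention participants enter through imputation and caseloads are 180/J, the 10-coach, ICC 0.02 case moves from 6.0% to 6.4%. Simulating the unadjusted t-test at 180 per arm (40,000 runs per cell) gave 6.3% for that case, and 8.5% for 10 coaches at ICC 0.05, where the formula gives 8.4%.

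**The case against.** The strongest reply is that the article names a model class and no more. It specifies no error structure or variance estimator for T1, and an e-coach term or clustered standard errors could be set in an analysis plan that is not shown. A reader might infer that the T1 model is declared to have independent errors. The text does not say that, and this point does not rest on it. The sentence on long-term effects can also be read as being about repeated measures, so it does not show that clustering at T1 was considered and rejected.

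A reader might also infer that the outcomes are clustered and that type I error is inflated. That needs an ICC above zero and a caseload, and the article gives neither. At ICC zero there is no inflation; at ICC 0.01 with 20 coaches it is 0.2 percentage points. Participants who never sign in have no coach, which dilutes clustering under intention-to-treat. The monthly contact over 12 months largely falls after T1 and bears on follow-up. The choice of training also depends on the provider's allocation rules and on participant preference.

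All of this limits how firmly and how large the point can be stated. It leaves three things standing: the nesting is in one arm and begins before T1; the article states a T1 model and a separate approach for follow-up without naming coaches in either; and the sample size demonstrably has no allowance.

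**Conclusion.** The point holds in conditional form. The stated T1 model and sample size make no allowance for e-coaches. If the e-coach ICC is above zero, an analysis that follows the stated T1 model without adding a coach term or clustered errors understates the primary standard error, in the direction that favours the intervention. With 6 to 20 coaches, about 130 evaluable intervention participants and ICC 0 to 0.05, the standard error ratio is 1.00 to 1.23 and one-sided error 5.0% to 9.1%; the upper end needs both the fewest coaches and the highest ICC. At 10 coaches and ICC 0.02, error is 6.0%, and clustering lowers power from 0.88 to 0.84. The documents do not support describing the inflation as established, or attributing the whole drop from 0.90 to clustering. This is a worthwhile, inexpensive improvement and does not invalidate the design.

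**What to change.** Before analysis, specify the T1 comparison as a partially nested linear mixed model:
- a random e-coach intercept in the intervention arm only;
- controls, and intervention participants who never signed in, entered as singletons;
- a separate residual variance for each arm;
- a small-sample correction to the degrees of freedom, such as Kenward-Roger.

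Use the same term in the follow-up models, where coach contact lasts longer. If the simpler model stays primary, prespecify this one as a sensitivity analysis. In either case, report the number of coaches and the estimated ICC.

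Recruitment has closed, so only the analysis can change. The data requirement is a coach identifier per participant, which should be obtainable because "e-coaches will be requested to complete the 10-item therapist version" of the alliance measure at T1 and T3. The costs are a slightly wider confidence interval, fewer degrees of freedom, and work to make the imputation respect the nesting and to pool the corrected degrees of freedom across imputed data sets. With few coaches and a small ICC, the coach variance may be estimated at zero, so the plan should say what is then reported.
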